### 3.7. Data Collection and Quality Assurance (STROBE: “Bias” and “Data Quality”)

Data will be collected using standardized forms and subsequently entered into a REDCap electronic database, ensuring traceability and version control. A double-entry procedure will be applied to minimize transcription errors. Measurement equipment, including the dynamometer and electromyography system, will be calibrated monthly according to internal technical control protocols. Evaluators will receive standardized training prior to study initiation, and inter-rater reliability will be verified using intraclass correlation coefficients (ICC) greater than 0.90 to reduce measurement bias and ensure the methodological quality of the study.

### 3.8. Ethical Considerations

The protocol was approved by the Research Ethics Committee (23/06/2025 CEIm Ref. 2025/07). Due to the vulnerable nature of this population, the consent process will emphasize clear and understandable language, adequate time for decision-making, voluntariness without impact on clinical care, the right to withdraw participation at any time, and the presence of an impartial witness in cases of limited literacy. Data will be anonymized and stored in encrypted databases in accordance with Regulation (EU) 2016/679 (GDPR), Organic Law 3/2018 on the Protection of Personal Data and guarantee of digital rights, and Law 14/2007 on Biomedical Research.

### 3.9. Statistical Analysis

The primary endpoint is the absolute change in dominant-hand handgrip strength (HGS) between hospital admission and discharge. The primary analysis will consist of a within-subject comparison of admission and discharge HGS values. Mean change scores and corresponding 95% confidence intervals will be reported. Statistical significance will be assessed using a paired *t*-test for normally distributed data or the Wilcoxon signed-rank test when normality assumptions are not met. All tests will be two-sided, with a significance level of *p* < 0.05. Exploratory longitudinal analyses will be performed using linear mixed-effects models to characterize daily trajectories of handgrip strength (HGS) and sEMG parameters during hospitalization while accounting for repeated measurements within participants and unequal numbers of observations across individuals. These analyses are intended to describe temporal patterns of muscle function and neuromuscular fatigue and are considered secondary and exploratory. They do not constitute the primary analysis of the study. Missing data due to discharge, clinical deterioration, medical procedures, symptom burden, or death will be handled under the missing-at-random (MAR) assumption inherent to mixed-effects modeling. The frequency and reasons for missing observations will be systematically documented across all outcome domains.

The primary endpoint is the absolute change in dominant-hand handgrip strength (HGS) between hospital admission and discharge. The primary analysis will consist of a within-subject comparison of admission and discharge HGS values. Mean change scores and corresponding 95% confidence intervals will be reported. Statistical significance will be assessed using a paired *t*-test for normally distributed data or the Wilcoxon signed-rank test when normality assumptions are not met. All tests will be two-sided, with a significance level of *p* < 0.05.

Associations between functional outcomes, sEMG parameters, and biomarkers will be explored using multivariable regression models adjusted for pre-specified covariates (age, sex, ECOG performance status, cancer type, comorbidity burden, and length of hospital stay). Given the exploratory nature of the study and the planned sample size, these analyses will be interpreted cautiously and will primarily serve to estimate effect sizes and identify candidate variables for future confirmatory studies. The contraction intensity used during each sEMG fatigue assessment (65% or 50% MVC) will be recorded and considered during data interpretation. Because contraction intensity may influence neuromuscular fatigue parameters, exploratory analyses will account for intensity level and, when sample size permits, stratified analyses will be performed. No direct comparison between intensity conditions is planned, and results obtained under different intensity levels will be interpreted cautiously.

Participants with both admission and discharge handgrip strength (HGS) measurements will be included in the primary endpoint analysis. The frequency and reasons for missing discharge assessments, including early discharge, transfer to another facility, clinical deterioration, or death, will be systematically documented.

Sensitivity analyses will compare baseline demographic and clinical characteristics between participants with complete and incomplete primary endpoint data. When appropriate, exploratory analyses based on the last available HGS measurement obtained during hospitalization will be conducted to assess the robustness of the primary findings. Results from these analyses will be interpreted cautiously due to the potential for informative missingness.

Hydration-related variables, including edema, ascites, and recent intravenous fluid administration, will be considered in the interpretation of bioelectrical impedance analysis (BIA)-derived outcomes and may be incorporated into sensitivity analyses when clinically relevant. Additional clinical variables may also be included in exploratory or sensitivity analyses when justified and supported by sufficient data availability.

Sensitivity analyses will be performed when substantial missing data or potential sources of bias are identified, to assess the robustness of the findings. Attention will be given to variables in which missingness may be related to clinical status or disease severity. Biomarker measurements obtained only when clinically indicated will be analyzed descriptively and interpreted with caution due to potential non-random availability across participants.

Overall, all association analyses are exploratory in nature and intended to generate hypotheses and provide preliminary estimates of potential relationships for future confirmatory studies. The number of repeated assessments may vary among participants depending on hospitalization duration and clinical feasibility.

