Prior to analysis, all recordings will undergo visual inspection and quality-control procedures. Signal segments will be excluded if they exhibit evidence of electrode displacement, signal saturation, excessive baseline noise, movement artifacts, abrupt signal discontinuities, or other technical abnormalities that may compromise signal interpretation. When multiple epochs are available, only artifact-free segments meeting predefined quality criteria will be included in the final analysis.

To ensure reliability in the bedside hospital setting, all evaluators will undergo standardized training, and all procedures will follow predefined operating protocols. Electrode placement sites will be systematically documented to ensure consistent positioning across repeated measurements.

Safety Monitoring and Adverse Event Recording

All assessments will be performed only when participants are considered clinically stable by the attending medical team. Prior to each testing session, patients will be screened for contraindications, including acute clinical deterioration, uncontrolled pain, severe fatigue, hemodynamic instability, active infection requiring urgent intervention, or any condition that may compromise safe participation.

Adverse events occurring during or immediately after testing will be documented, including dizziness, excessive fatigue, pain exacerbation, musculoskeletal discomfort, cardiovascular symptoms, falls, or any unexpected clinical event. The severity, duration, and relationship to the assessment procedure will be recorded.

Testing will be immediately discontinued if participants report intolerable discomfort, request termination, exhibit signs of excessive fatigue, develop cardiovascular symptoms, or if the research team determines that continuation may compromise safety. Participant safety will always take precedence over protocol completion.

Serum biomarkers—Basic Panel

Laboratory assessments will be performed at hospital admission and discharge. In cases where daily blood tests are required for clinical reasons, these additional results will be incorporated into the longitudinal analysis.

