### 3.6. Criteria for Suspending/Omitting Measurements

Measurements will be suspended in the presence of fever > 38 °C, symptomatic hypotension, moderate-to-severe pain, nausea, or clinical events that compromise participation. The possibility of omitting measurements on specific days is considered part of the ethical and pragmatic management of research in hospitalized oncology patients.

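### Days withheld for same-day illness are treated as missing at random, so the exploratory daily grip curve describes days fit for testing, not all hospital days

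*Protocol article*

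**What the plan says.** Section 3.5 plans handgrip and sEMG tests every day from Day 2 to the penultimate day of the stay. Section 3.3.1 makes the daily handgrip values, collected throughout hospitalization, a secondary exploratory outcome describing how muscle deterioration unfolds over time.

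Two passages decide whether a test takes place on a given day:
- Section 3.6: "Measurements will be suspended in the presence of fever" above 38 °C, "symptomatic hypotension, moderate-to-severe pain, nausea, or clinical events that compromise participation". It adds: "The possibility of omitting measurements on specific days is considered part of the ethical and pragmatic management".
- Section 3.4, Safety Monitoring and Adverse Event Recording: before each session the patient is screened for conditions that include "acute clinical deterioration, uncontrolled pain, severe fatigue, hemodynamic instability, active infection requiring urgent intervention".

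Section 3.9 analyses the daily data with linear mixed-effects models. It names discharge, clinical deterioration, medical procedures, symptom burden and death together as causes of missing data, all under one assumption: "symptom burden, or death will be handled under the missing-at-random (MAR) assumption inherent to mixed-effects modeling". Later it adds: "Sensitivity analyses will be performed when substantial missing data or potential sources of bias are identified". No method is named there for the daily curve. Section 6 concedes that informative missingness may affect the longitudinal analyses.

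**The concern.** This is about days on which the patient is still in hospital but is not tested. It is not about days after discharge or death.

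Missing at random is not a property of the mixed model. It is a condition on the data: given the observed grip values and whatever the model contains, being untested must not depend on the value that would have been measured. Here the protocol itself writes the rule that creates the gaps, and the rule acts on that day's fever, pain, nausea, hypotension or severe fatigue. A maximal voluntary grip on such a day would plausibly be lower than on the patient's other days. The likely departure is therefore known before any data are collected.

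At stake is the reading of the daily handgrip trajectory. If it is read as grip over all hospital days, its level is too high. If holds become more or less frequent over the stay, its slope is also off, in a direction that depends on the timing.

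**Working it through.** **1. The passages side by side.** The hold rules (3.6 and the safety text in 3.4) make testing depend on same-day state. Section 3.9 assigns gaps from clinical deterioration and symptom burden to missing at random, in the same list as gaps from medical procedures, which may well be unrelated to that day's strength. Reasons for missed tests are to be recorded (3.9, section 4), but no stated analysis uses them to separate the two kinds of gap. The analysis of the last available handgrip value in 3.9 serves the primary endpoint, not the daily curve.

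**2. Size, closed form.** The plan has no figure to reproduce. All inputs here are assumptions: within-patient day-to-day SD s = 2–3 kg, correlation of same-day illness with same-day grip r = 0.3–0.7, 10-day stay, no true trend. Take illness as standard normal and withhold the test when it exceeds the cut-off c that removes a share p of days. Mean grip on tested days then exceeds mean grip on all days by

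r × s × φ(c)/(1 − p),

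with r × s between 0.3 × 2 = 0.6 kg and 0.7 × 3 = 2.1 kg.

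| Share withheld p | c | φ(c) | φ(c)/(1 − p) |
|---|---|---|---|
| 5% | 1.645 | 0.1031 | 0.109 |
| 10% | 1.282 | 0.1755 | 0.195 |
| 20% | 0.842 | 0.2800 | 0.350 |
| 30% | 0.524 | 0.3477 | 0.497 |
| 40% | 0.253 | 0.3863 | 0.644 |

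- 20% withheld evenly: level too high by 0.6 × 0.350 = 0.21 kg to 2.1 × 0.350 = 0.74 kg. The slope is not biased.
- 40% falling to 5%: change in bias 0.644 − 0.109 = 0.535, so a false decline of 0.6 × 0.535 = 0.32 kg to 2.1 × 0.535 = 1.12 kg over the stay.
- 30% falling to 10%: 0.497 − 0.195 = 0.302, so 0.18 to 0.63 kg.
- 5% rising to 40%: the same 0.32 to 1.12 kg with the opposite sign, a false improvement that would mask a real decline.

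**3. Check with a fitted mixed model.** Simulation with a random intercept and a linear day effect: stays of 5–10 days, symptom-free slope −0.2 kg/day, residual SD 1.5 kg, a deficit of 1, 2 or 4 kg on symptom days, every symptom day withheld (8 runs of 150 patients per setting). These inputs are also assumptions. Between 21% and 29% of days were withheld.
- Mid-stay level too high by about 0.3, 0.5 and 1.0 kg for deficits of 1, 2 and 4 kg.
- Holds constant at 25%: fitted slope within about 0.007 kg/day of the all-days slope.
- Holds rising from 10% to 40%: all-days slope −0.23, −0.27, −0.33 kg/day; fitted −0.19, −0.21, −0.22. Decline is understated.
- Holds falling from 40% to 10%: all-days slope −0.16, −0.14, −0.07 kg/day; fitted −0.19, −0.21, −0.21. Decline is overstated.

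The fitted slope stayed near the symptom-free −0.2 kg/day throughout: the model recovers the fit-for-test curve.

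**4. Scale.** For orientation only, the 95% confidence half-width of the primary mean change with n = 50 and the plan's SD of 4–5 kg is 2.01 × 4/√50 = 1.14 kg to 2.01 × 5/√50 = 1.42 kg. It comes from a different analysis and is not the standard error of the trajectory.

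**The case against.** The protocol does not hide the issue. Section 6 concedes possible informative missingness for these models. Section 3.9 promises conditional sensitivity analyses, with attention to missingness related to clinical status, and allows further clinical variables. The daily models are labelled exploratory throughout. Details of a not-at-random method commonly belong in a statistical analysis plan, which is not at hand. And if the target is strength when the patient can be tested, the fitted curve is close to that target; reduced effort during fever is arguably not muscle deterioration.

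Much of this stands, and it sets the weight of the point. It does not remove it. The article affirmatively places gaps from symptom burden under missing at random; that stated choice is the subject, not an absent detail. The trigger for sensitivity analysis waits for a source of bias to be identified, when the hold rules already identify one. The last argument supports a label that the protocol does not give.

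Four stronger readings are tempting, and the documents do not support them:
- *The defect is that symptoms are left out of the model.* Section 3.9 lists no covariates for the mixed model; the list of age, sex, ECOG, cancer type, comorbidity and length of stay belongs to the multivariable regressions. Nor would a symptom indicator repair the problem if holds are absolute, since no grip is then seen on symptom days.
- *The model fills in the withheld days as average days.* A likelihood-based mixed model fills in nothing; it estimates from the observed days.
- *The daily trend will be false.* With a constant hold rate the slope is almost unaffected.
- *The sEMG trajectories are biased in the same way.* No direction or size has been shown for median frequency, mean frequency or fatigue slope.

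**Conclusion.** The point holds for the exploratory daily handgrip trajectory. For gaps caused by clinical holds, missing at random does not follow from the design, and the fitted curve should be read as grip on days fit for testing. Under the assumed inputs the effect on level is tenths of a kilogram, and the effect on trend reaches about 1 kg over the stay only with a steep time gradient in holds and the upper end of the assumed SD and correlation. The hold rate, its time pattern, the within-patient SD and the illness–grip correlation are all assumed; only the direction of the level bias follows from the hold rules, and then only if same-day illness lowers same-day grip.

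A reader might infer that the main result is compromised. It is not by this route: the primary analysis is a paired comparison of admission and discharge and does not use the mixed model. The change is worth making because it is cheap and alters how a reported curve is read, not because the study's main conclusion depends on it.

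**What to change.** In section 3.9:
- Classify in-stay gaps, by the reason already recorded, into clinical holds (section 3.6 and the safety text in 3.4) and logistic misses such as procedures or scheduling. Keep the missing-at-random assumption for logistic misses only.
- Label the mixed-model handgrip curve as grip on days fit for testing. Beside it, show by hospital day the share of patients withheld for clinical reasons, so that a changing hold rate is visible.
- If the curve is also to be read as grip on all hospital days, replace the conditional sensitivity wording, for clinical holds, with a pre-specified delta-adjusted analysis: impute withheld days at, for example, 0, 1, 2 and 4 kg below the missing-at-random prediction and report all four.

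The cost is a few sentences and a little programming. Reasons for missed tests are already collected, so no new data are needed. The downside is that an all-days trajectory is then reported as a range instead of one curve. The clinical hold rules stay unchanged.

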The sample size was estimated based on the expected change in HGS, defined as the difference between admission and discharge in the dominant hand, which constitutes the primary outcome. A clinically meaningful difference of 4–5 kg was assumed, based on previous studies in oncology populations, with a standard deviation of 4–5 kg for change in HGS, consistent with prior literature in cancer and comparable adult populations [13].

Using a two-sided significance level of 0.05 and a statistical power of 80%, the estimated minimum sample size ranged between 16 and 25 participants. However, given the exploratory and hypothesis-generating nature of the study, a larger sample size was selected to improve precision and robustness of estimates. A target sample of 50 participants was therefore established. Assuming a potential dropout rate of approximately 10%, the study aims to recruit 55 participants in total. The recruitment period was established based on the expected volume of oncology admissions at the participating institution and previous clinical experience with similar patient populations. Considering the anticipated number of eligible admissions and the target sample size of 55 participants, the planned recruitment window from March to November 2026 is considered feasible. Recruitment feasibility is supported by the high volume of oncology admissions managed by the Medical Oncology Department of the Complejo Asistencial Universitario de Salamanca, a tertiary referral center serving multiple health areas. Although precise screening figures are not available, previous institutional activity suggests that recruitment of 55 participants within the planned recruitment period is achievable.

This approach is consistent with phase II signal-seeking or feasibility study designs, aiming to obtain more stable estimates of HGS changes and variability, reduce the impact of missing data, and enable exploratory multivariable analyses of limited complexity, in line with methodological recommendations for pilot and feasibility studies [14,15,16,17,18]. Daily repeated measurements will not be included in the sample size calculation and will be analyzed as exploratory longitudinal outcomes.

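### The primary grip-strength change is a complete-case mean although missing discharge tests are tied to clinical state, and the one estimate named as a robustness check can share its bias

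*Protocol article*

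**What the plan says.** Section 2.1 of the protocol article sets out to quantify the change in dominant-hand grip strength (HGS). Section 3.9 defines the endpoint ("The primary endpoint is the absolute change in dominant-hand handgrip strength (HGS) between hospital admission and discharge") and the test ("Statistical significance will be assessed using a paired *t*-test for normally distributed data or the Wilcoxon signed-rank test when normality assumptions are not met"). It then fixes the analysis set: "Participants with both admission and discharge handgrip strength (HGS) measurements will be included in the primary endpoint analysis". As reasons for a missing discharge test it lists early discharge, transfer, clinical deterioration and death.

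Two other parts of the plan decide who gets tested. Section 3.4, under safety monitoring, says: "All assessments will be performed only when participants are considered clinically stable by the attending medical team". Section 3.6 suspends measurements for fever, symptomatic hypotension, moderate-to-severe pain, nausea or other clinical events that compromise participation.

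For incomplete primary data, section 3.9 offers two things. One is a comparison of baseline characteristics between complete and incomplete cases. The other applies only where judged appropriate: "exploratory analyses based on the last available HGS measurement obtained during hospitalization will be conducted to assess the robustness of the primary findings". The same section plans a linear mixed model on daily HGS, labelled secondary and exploratory, with this rule: "Missing data due to discharge, clinical deterioration, medical procedures, symptom burden, or death will be handled under the missing-at-random (MAR) assumption". It also allows unspecified sensitivity analyses if missing data are substantial. Sections 3.9 and 6 acknowledge that missingness may be informative.

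**The concern.** Whether a discharge value exists depends on how the patient is doing, and so does grip strength. A mean over patients with both values then describes those well enough, and in the ward long enough, to be tested on the day they left. Because the objective is the size of the change, an error in the mean damages the answer even if the test against zero is unaffected.

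The named checks do not settle this. The baseline comparison gives no estimate of change. The last-available-value analysis gives one, but for a patient who deteriorates the last value tends to come before the deterioration, because testing stops when the patient becomes unstable. It can then agree with the complete-case result and be read as confirming it. The mixed model uses the daily values but is not directed at the admission-to-discharge change. Its missing-data rule also counts discharge and death as causes of data missing at random (MAR), although no inpatient grip value exists after either event.

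**Working it through.** **Inputs from the documents (section 3.2).** SD of change 4–5 kg; meaningful difference 4–5 kg; target 50; dropout about 10%; 55 recruited; two-sided 0.05; 80% power.

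**The plan's own figures.** 50 × 1.10 = 55, as stated. The stated minimum of 16 to 25 reproduces as n = 2(1.960 + 0.842)² (SD/δ)²: 15.7, so 16, for SD/δ = 1; and 24.5, so 25, for 5/4. This is the formula for two independent groups. The planned test is paired and would need 8 to 13 by the normal formula. The stated figure is therefore conservative, and this does not affect the present point.

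**Precision.** Half-width = t(0.975, n−1) × SD/√n. At n = 50 it is 1.14 kg (SD 4) to 1.42 kg (SD 5). At n = 45 it is 1.20 to 1.50, and at n = 40 it is 1.28 to 1.60.

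**Bias.** Let c be the completers' mean change, m the missing share, and g the mean change in missing patients minus that in completers (negative means worse). The mean over everyone is (1−m)c + m(c+g) = c + mg, so the complete-case error is −mg. The documents do not give g, so the values below are assumptions. A positive error means decline understated.

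| Assumed g (kg) | m = 10% | m = 20% | m = 30% |
|---|---|---|---|
| −2 | +0.2 | +0.4 | +0.6 |
| −5 | +0.5 | +1.0 | +1.5 |
| −8 | +0.8 | +1.6 | +2.4 |
| +2 | −0.2 | −0.4 | −0.6 |
| +4 | −0.4 | −0.8 | −1.2 |

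The two kinds of missingness can offset each other. With g = −5 for deteriorators and +3 for early dischargees, 10% of each gives 0.10×5 − 0.10×3 = +0.2 kg. With 15% and 5% the error is +0.6 kg; with 5% and 15% it is −0.2 kg.

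**How the planned analyses behave.** Illustrative simulation, all settings assumed: 55 patients; 8 daily tests; mean change −4 kg; SD of the true change 3.6 kg; measurement SD 1.9 kg, so the SD of observed change is √(3.6² + 2×1.9²) = 4.5 kg, inside the plan's range; 20% without a final value; 25 runs per row. Mean change in kg:

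| Who is missing | All patients | Complete case | Last value | Mixed model |
|---|---|---|---|---|
| At random | −3.77 | −3.76 | −3.34 | −3.78 |
| Those whose observed values fell | −3.91 | −3.10 | −3.53 | −3.94 |
| Those with a steeper underlying slope | −3.96 | −3.12 | −3.15 | −3.49 |
| The better patients | −4.07 | −4.97 | −4.02 | −4.54 |

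The Monte Carlo error of each entry is about 4.5/√55/√25 = 0.12 kg. Columns in a row share the same simulated data, so differences between them are more precise. The target is the day-8 change in everyone, so the last row stands in only roughly for early discharge.

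In the third row, complete case and last value differ by 0.03 kg while both miss the all-patient mean by about 0.8 kg. The check looks reassuring when it should not. The mixed model is closer than complete case in all three rows with selective missingness, but it still misses by about 0.47 kg in the third and fourth, because missingness there depends on slopes that the observed values reveal only in part.

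**The case against.** The strongest defence has five parts.

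- **Direction.** A reader might infer that the decline will be understated. The documents do not support that. Early discharge and transfer are listed beside deterioration and death, no split is given, and the sign reverses if better patients are missing. In that case the last-value analysis did well (−4.02 against −4.07) and the mixed model did worse (−4.54). This stands.
- **Other estimates exist.** A reader might infer that the last-value analysis is the plan's only fallback that yields an estimate. It is not: section 3.9 also plans the daily mixed model and an open sensitivity provision. What remains is that the model is not tied to the primary change and the open provision names no method. The last-value analysis also keeps patients who have a later in-hospital value and can recover part of the bias, as in the second row of the simulation.
- **Sample size wording.** Section 3.2 says the larger sample should "reduce the impact of missing data". A reader might take this as a claim that numbers cure bias. It stands beside the dropout allowance and the aim of more stable estimates, and is fairly read as protecting precision. It is no error.
- **Disclosure and status.** The plan admits possible informative missingness, for the primary outcome too, and calls itself exploratory. That lowers the severity. But no named analysis of the primary change relaxes the assumption.
- **Level of detail.** Delta values and the trigger for the conditional analysis may belong in an analysis plan that is not shown. The point therefore rests on what the article fixes: the complete-case set, the conditional last-value check, the descriptive role of the mixed model, and discharge and death under MAR. The article does describe trajectories as in-hospital, so the last item is partly met.

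**Conclusion.** The point holds in a limited form. The complete-case mean may be biased in a direction that the documents do not settle, and the one estimate named as a robustness check can share the bias when decliners are the ones missing.

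At the planned 10% missing the bias is modest: 0.2 to 0.8 kg for assumed differences of 2 to 8 kg, below the half-width of 1.14 to 1.42 kg. At 20% it is 0.4 to 1.6 kg and can match or exceed that half-width. If the missing patients do 2 to 4 kg better, decline is overstated by 0.2 to 0.4 kg at 10% and 0.4 to 0.8 kg at 20%.

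These sizes rest on assumed differences. They also do not cover deaths, for whom no end-of-stay grip value is defined.

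The test against zero is not the weak spot if the decline is as large as planned. With a completers' mean of −4 kg and 10% missing, the overall mean reaches zero only if g = 4/0.10 = +40 kg. What is exposed is the size of the change, which is the stated objective. Severity is moderate.

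**What to change.** 1. Keep the paired analysis. Always report beside it, as a prespecified sensitivity analysis of the primary endpoint, the mean change from admission to each patient's last inpatient day. Take it from a mixed model on all daily dominant-hand HGS values in every patient with an admission value. Section 3.5 already schedules these measurements.
2. Because that model still assumes MAR, add a delta (tipping-point) analysis for patients without a discharge value. Allow worse values after deterioration or transfer and better values after early discharge, and show the mean change over the range. Keep the last-available-value analysis only as a supplement.
3. Report deaths separately and state how they enter the target quantity. Do not treat days after death or discharge as values missing at random; confine trajectory statements to days alive and in hospital.

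The cost is a change of wording and a modest amount of extra analysis, with no new data. The downside is reliance on the mixed model's assumptions about the shape of the trajectory and about missingness, which is why the delta analysis should go with it.
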